## Abstract

**Background:**

Low therapeutic adherence to medication is very common. Clinical effectiveness is related to dose rate and route of administration and so poor therapeutic adherence can reduce the clinical benefit of treatment. The therapeutic adherence of patients with chronic obstructive pulmonary disease (COPD) is extremely poor according to most studies. The research about COPD adherence has mainly focussed on quantifying its effect, and few studies have researched factors that affect non-adherence. Our study will evaluate the effectiveness of a multifactor intervention to improve the therapeutic adherence of COPD patients.

**Methods/Design:**

A randomized controlled clinical trial with 140 COPD diagnosed patients selected by a non-probabilistic method of sampling. Subjects will be randomly allocated into two groups, using the block randomization technique. Every patient in each group will be visited four times during the year of the study. Intervention: Motivational aspects related to adherence (beliefs and behaviour): group and individual interviews; cognitive aspects: information about illness; skills: inhaled technique training. Reinforcement of the cognitive-emotional aspects and inhaled technique training will be carried out in all visits of the intervention group.

**Discussion:**

Adherence to a prescribed treatment involves a behavioural change. Cognitive, emotional and motivational aspects influence this change and so we consider the best intervention procedure to improve adherence would be a cognitive and emotional strategy which could be applied in daily clinical practice. Our hypothesis is that the application of a multifactor intervention (COPD information, dose reminders and reinforcing audiovisual material, motivational aspects and inhalation technique training) to COPD patients taking inhaled treatment will give a 25% increase in the number of patients showing therapeutic adherence in this group compared to the control group.

We will evaluate the effectiveness of this multifactor intervention on patient adherence to inhaled drugs considering that it will be right and feasible to the clinical practice context.

**Trial registration:**

Current Controlled Trials ISCTN18841601

## Background

As with all chronic diseases, non-adherence in patients with COPD is common and contributes to adverse health outcomes, reduced quality of life and increased healthcare expenditures [1]. According to the World Health Organization (WHO), patient adherence to long term therapy averages 50 percent [2]. Adherence rates in clinical trials may be as high as 70 to 90 percent [3-5], but in clinical practice it is in the range of 10 to 40 percent [6-8]. In the Lung Health Study [3,9], therapeutic adherence with inhaled treatment recorded by self-reported methods after a one year follow-up was 60 percent and decreased to 50 percent at the five year follow-up.

Despite the research about treatment adherence, few factors have been associated with it [1]. Characteristics of COPD medications and regimens can contribute to non-adherence; several studies have reported that an average of 60 percent of patients with COPD do not follow the prescribed therapy [10]. Patients with COPD often have medication for other pathologies and polypharmacy is a common contributor to poor adherence. Another factor is the frequency of dosing for every drug, the more doses they have, the lower the adherence can be. Patients taking multiple medications, each one with a different dosing pattern, can be confused and frustrated by this and it can lead to forgetting to take medications. The route of administration can also influence adherence. The oral forms are easier and have higher adherence than inhaled medications [11]. In addition, mistakes in inhalation techniques are frequent and they too affect adherence; several studies have reported that up to 85 percent of patients use their inhaler ineffectively [10]. Another problem is the drug's efficacy; adherence is higher to a drug whose pharmacological effect is quick and has a direct impact on symptoms. Additional factors can include adverse side effects and, in some healthcare systems, the inability to pay or a reduced access to medication [12].

There are factors related with patients that can influence adherence such as age. Adherence is often better in older persons, but the increase of age is also associated with comorbidity, polypharmacy, cognitive decline and in some cases, with difficulty in reading small print or to open and manage the devices. Another factor is the patient's disease perception that leads to the discontinuation of therapy due to a lack of or excess of clinical symptoms, inconvenient or expensive medication [12]. This perception is built up by the patient and also by the healthcare provider and caregivers.

There are few studies about interventions to improve therapeutic adherence in COPD patients and other important aspects of the disease management. Most of them have been joint studies with asthmatic patients [13-18]. They have mainly focussed on quantifying the adherence and not many have explored factors which affect non-adherence, although the authors point out the need for working in motivational and cognitive ways to improve patients' understanding of both their illness and treatment [18].

Specific studies which consider educational programs exclusively for COPD patients, show significant improvement in patients' management of disease, less exacerbations, decrease in the rescue medication and improved knowledge about inhaler use [15,17]. These programs include information about the illness, the treatment, the importance of the adherence, the management of exacerbation, instructions about the inhalation technique, and recommendations about the proper time to ask for doctor's advice and, in some cases, counseling to cease smoking or referrals to independent programs.

Between 1998 and 2003 our research team carried out a cohort study of patients with COPD in two health centers in Malaga. The Batalla Test [19], the Morinsky-Green test [20] and the self-reported compliance from Haynes and Sackett test [21] were all included as treatment adherence evaluation methods. We found little consistent data. Between 2004 and 2006, we performed another cohort study in 195 COPD patients from 4 health centers. Patients have been followed up during 1 year and we have used four therapeutic adherence measures: the Batalla test, the Morinsky-Green test, the Haynes-Sackett test and the dose/pill count. In this study we selected the dose/pill count as the reference method to measure adherence and we calculated the diagnostic validity of the self-reported methods. We found that the use of the Batalla test and the Morisky-Green test together was the most reliable way to assess adherence by self-reported methods and we proposed a strategy to measure adherence in clinical practice depending on the adherence prevalence [22]. Taking all this into account, our next step in the study of adherence was the design of a multifactor intervention to improve treatment adherence in patients with COPD.

The main objective of this study is to evaluate the effectiveness of a multifactor intervention (COPD information, dose reminders, audiovisual material, motivational aspects and inhalation techniques training) to improve the therapeutic adherence in COPD patients with inhaled scheduled treatment after one year follow-up with two reinforcement visits (3 and 6 month after intervention). The second objective is to describe the main factors related to adherence. The specific aims are:

- To evaluate in two study groups treatment adherence prevalence with inhaled medication (primary outcome variable) at the beginning of the study, at three and six months and at one year after the intervention.

- To evaluate the functional status using a forced spirometry and the quality of life (St George Respiratory questionnarie, EuroQoL-5D) and the clinical progress (SeguiEPOC) as secondary outcome measures in both groups.

- To analyse the main factors related to therapeutic adherence.

## Methods

This study has been approved by the Ethical Committees of Distrito Sanitario Málaga (01/03/07) and Axarquía (13/05/08) and by Committee of Clinical Trials of Hospital Clínico Universitario Virgen de la Victoria (30/11/07). The study protocol was reviewed by Spanish Medicine Agency and Sanitary products.

### Participants

140 patients with COPD selected by a non-probabilistic consecutive sampling method. The inclusion criteria were searched in the patient's clinical record as: having been diagnosed of COPD by spirometry following the SEPAR (Sociedad Española de Neumología y Cirugia Torácica) guidelines [23], receiving clinical assistance in primary care centers in Malaga area, having been prescribed inhaled and scheduled treatment; and having agreed to be part of the study by giving signed written consent. Exclusion criteria: other respiratory conditions which are not included in the COPD definition (bronchiectasis, asthma or cystic fibrosis) and cognitive impairment problems registered in their clinical record (Dementia, Alzheimer, Parkinson, Cognitive decline).

### Sample size

it was calculated to detect an adherence percentage difference between the two groups of 25%, with a statistical power of 80% and a confidence level of 95%, assuming a percentage of expected losses of 15%. The final sample size was 140 patients with COPD that meet the selection criteria mentioned above.

### Design

Randomized controlled clinical trial. (Figure 1)

**Figure 1 F1:**
[figure not shown]
**Study general graphic**.

### Setting

Primary Care

### Outcomes

#### Primary outcome

the therapeutic adherence considered as the percentage of patients classified as good adherent. The adherence will be measure by three adherence measurements: the Morinsky-Green test (MGT) [20], the Batalla test (BT) [19] and the dose/pills count. We will consider as reference methods the results of dose/pill count. Each method will be considered independently.

The MGT measures the attitude towards treatment and it was adapted by us to inhaled medication. The test has four questions and a patient will be considered a good adherent when he answers properly the complete questionnaire.

The BT provides information about the patients' knowledge of their illness. The test has three questions, adapted to COPD, and a patient will be considered a good adherent when he answers properly the complete questionnaire.

The dose/pill count is the number of pills or doses taken divided by the number of pills or doses prescribed, multiplied by 100 (expressed as a percentage). According with Sackett et al. [21] recommendations, a good adherence is considered when the result of counting is between 80% (a twenty percent of doses/pills missed) and 110% (the patient inhales a ten percent more of doses/pills) of dose/pill prescribed. This cutoff point was selected for consistency with other studies [24-26].

We consider the dose/pill count as the more confident method. We use the two self-reported methods because they are easier to apply in clinical practice and, in a previous work conducted by us, we found acceptable indicators of their validity as diagnostic test for treatment adherence in COPD patients under certain environment circumstances.

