### Statistical Analysis

A descriptive statistical analysis will be performed for all the study variables. We will calculate the mean, median and standard deviations for quantitative variables, and the absolute and relative frequency for qualitative variables.

The 95% confidence level will be applied. The analysis will be made under an intention-to-treat procedure. The between-group comparison for the primary outcome will be explored using the Chi Square Test. The Relative Risk Reduction (RRR), the Absolute Risk Reduction (ARR) and the Number Needed to treat (NNT) will be calculated. Inferences for the secondary outcomes will be made using an analysis of variance (ANOVA). Finally a logistic regression model will be performed for the primary outcome [treatment adherence (yes/not)], considering the intervention as the predictive variable and the rest of the independent measures as the possible modifying factors. We will use the usual 5% significance level (α = 0.05) and the SPSS statistical package, version 15.0, to run the proposed analysis.

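### Three adherence measures share the primary outcome and no text says which one, at which visit, decides the trial; dose/pill count at one year is only implied

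*Protocol article*

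**What the plan says.** - **Methods.** Protocol article, Primary outcome: the outcome is the percentage of patients classed as good adherents, and "The adherence will be measure by three adherence measurements". These are the Morisky-Green test, the Batalla test and the dose/pill count. The count is called the reference and the method the team trusts more; the section then adds "Each method will be considered independently". The Secondary outcome section covers spirometry, quality of life and clinical progress, and neither questionnaire is moved there.
- **Visits.** Background: the main objective is set after one year of follow-up. The specific aim that carries the primary-outcome label lists it "at the beginning of the study, at three and six months and at one year after the intervention". The Follow up section says adherence is measured at each visit in order to follow its course.
- **Test.** Statistical Analysis: "The between-group comparison for the primary outcome will be explored using the Chi Square Test", and "We will use the usual 5% significance level". Neither sentence names a method or a visit, and no adjustment for several comparisons is mentioned.
- **Size.** Sample size: "it was calculated to detect an adherence percentage difference between the two groups of 25" percent, again with no method or visit named.

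**The concern.** The analysis section speaks of one primary comparison, but the outcome section supplies three yes/no variables that fit the description, each measured at three visits after randomisation. Whoever runs the analysis has to choose, and nothing in the article binds that choice before results are seen.

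The three measures are not interchangeable. By the article's own account the Batalla test captures what patients know about their illness and the Morisky-Green test their attitude to treatment; only the count reflects doses taken. The intervention teaches disease information directly, through a presentation and a written dossier. Batalla could therefore improve while doses taken do not, and as the text stands that result could be reported as improved adherence on the primary outcome. Two things are at stake: the false-positive rate of the main claim, and what a positive trial would mean if the methods disagree.

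**Working it through.** **1. The plan's own figure.** Inputs from the Sample size section: a 25-point difference, 80% power, 95% confidence, 15% losses, total 140. Allocation is 1:1 (Recruitment). Two assumptions are needed: a two-sided test, and the control-arm rate, which the section does not give. The range 25-50% is used; 40% matches the Background statement that about 60% of patients do not follow therapy.

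n per arm = [z(0.975)·√(2·p̄·(1−p̄)) + z(0.80)·√(p1(1−p1) + p2(1−p2))]² / d²

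With p1 = 0.40, p2 = 0.65, p̄ = 0.525, d = 0.25: (1.960·√0.49875 + 0.842·√0.4675)² / 0.0625 = 61.4, so 62 per arm and 124 in total. Multiplying by 1.15 gives 143; dividing by 0.85 gives 146.

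| Assumed control rate | Per arm | Total after losses (×1.15 to /0.85) |
|---|---|---|
| 25% or 50% | 58 | 134-137 |
| 30% or 45% | 61 | 141-144 |
| 35% or 40% | 62 | 143-146 |

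The stated 140 lies inside 134-146. It fits one two-sided 5% test and leaves no allowance for several.

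**2. Error rate if more than one comparison may count.** For k independent tests, the chance of at least one false significant result is 1 − 0.95^k two-sided, and 1 − 0.975^k towards benefit.

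- k = 3: 1 − 0.95³ = 14.3%; 1 − 0.975³ = 7.3%.
- k = 9: 1 − 0.95⁹ = 37.0%; 1 − 0.975⁹ = 20.4%.

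The measures are taken on the same patients, so the test statistics will be correlated. The article gives no correlations; those below are assumed. Values come from multivariate-normal simulation. For nine tests, the same correlation is assumed between methods and between visits, and the two are multiplied when both differ.

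| Assumed correlation | Three methods, one visit: two-sided / benefit | Three methods × three visits: two-sided / benefit |
|---|---|---|
| 0 | 14.3% / 7.3% | 37.0% / 20.4% |
| 0.5 | 12.5% / 6.2% | 29.5% / 15.0% |
| 0.7 | 11.0% / 5.4% | 22.6% / 11.4% |
| 0.9 | 8.4% / 4.2% | 13.6% / 6.8% |

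With dose/pill count at one year as the only deciding test, the rates are 5% and 2.5%.

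**3. Cost of keeping all comparisons primary.** With Bonferroni control and a 40% control rate, three tests at 0.05/3 = 0.0167 need 83 per arm, or 191-196 in total after losses. Nine tests at 0.05/9 = 0.0056 need 103 per arm, or 237-243. With about 60 evaluable patients per arm (140 × 0.85 = 119), power is about 79% at 0.05, 64% at 0.0167 and 49% at 0.0056.

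**The case against.** The best defence is that the article already points to one comparison. It ranks dose/pill count above the questionnaires, explains the questionnaires by their ease of use in practice, sets the main objective at one year, describes months 3 and 6 as reinforcement visits, and gives monitoring as the reason for repeated measurement. The independence sentence may mean only that each method is scored by itself and not merged into a composite. The analysis section uses the singular, and 140 fits a single test. Multiplicity rules are also commonly left to an analysis plan, which is not shown.

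Much of this stands, and it limits the point. A reader might infer that the plan has no leading comparison, or that it commits to nine chi-square tests with a false-positive risk up to 37%. The documents support neither: a leading comparison is implied, and no sentence says every method is tested at every visit. A reader might also take the two-sided rates as the risk of falsely claiming improvement; that risk is about half as large. Nor does the inconsistency reported from the 1998-2003 cohort show that the count and the questionnaires disagree, because only self-report tests are listed for that cohort.

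What the defence does not settle is which result decides. In the Background, the team uses the reference-method label for a standard against which self-report was validated; that is not a rule for judging a trial. All three methods remain under the primary heading, and the independence sentence directly follows the one naming the reference. This is a tension within the stated text, beyond detail deferred to another document.

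**Conclusion.** The point holds in limited form. Dose/pill count at one year is the implied leading comparison but is not designated as the one that decides, and there is no rule for discordant results. If any of the three methods at one year may carry the claim, the chance of at least one false significant result is about 8-14% two-sided, or about 4-7% towards benefit against a nominal 2.5%. Nine tests are an upper bound that the text does not state: about 14-37% two-sided and 7-20% towards benefit. These ranges rest on assumed correlations from 0.9 down to 0 and on two-sided 5% tests; the document gives no correlations. The interpretive problem does not depend on them: as written, a gain in illness knowledge or attitude alone could be presented as success on the primary outcome.

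**What to change.** - In Primary outcome and Statistical Analysis, state that the single primary comparison is the proportion of good adherents by dose/pill count (80-110%) at the 1-year visit, tested once at two-sided 5%.
- Make the Morisky-Green and Batalla results, and all 3- and 6-month results, secondary or supportive, reported with confidence intervals.
- Reword the independence sentence to say only that the methods are scored separately.
- Tie the 25-point difference in Sample size to the same method and visit.

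This takes a few sentences, follows preferences the article already states, needs no new data and leaves 140 patients unchanged. It should be settled before any between-group result is seen. The small downside is that a positive self-report result alone would no longer make the trial positive.

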##### Group session

the session will last 2 hours including the patient's reception, the material distribution, the intervention and the farewell. The intervention is structured in three parts: the first part will be conducted following the focus group methodology. The number of patients will be about 6 to 9 per group. In the second part, patients will receive information about their disease and treatment with the aid of the distributed material. The third part will be conducted as a training session about inhalation technique.

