##### Cognitive Aspects

Information is given about the disease so the patients can get to know it better and be more conscious about the importance of the scheduled treatment.

We have designed an audiovisual presentation to inform the patients about the most important issues of their illness and its treatment and a written dossier with the oral presentation content which will be given to the patient.

In the follow-up visit we will ask the patient if he has doubts about his illness or about the information he was given in the group session. Any questions they have are answered straightaway.

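### The Batalla test, a knowledge test, is one of three separate primary adherence measures although only the intervention arm is described as being taught about COPD, so a gain on it may reflect learning rather than more doses taken

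*Protocol article*

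**What the plan says.** Under Primary outcome, the protocol article defines therapeutic adherence as the percentage of patients classed as good adherents. It then says: "The adherence will be measure by three adherence measurements", namely the Morisky-Green test, the Batalla test and the dose/pill count. On their relation it says "We will consider as reference methods the results of dose/pill count" and "Each method will be considered independently".

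On the Batalla test it says "The BT provides information about the patients' knowledge of their illness", and sets the rule: "The test has three questions, adapted to COPD, and a patient will be considered a good adherent when he answers properly the complete questionnaire". On the Morisky-Green test: "The MGT measures the attitude towards treatment and it was adapted by us to inhaled medication".

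Under Group session, in the second part, "patients will receive information about their disease and treatment with the aid of the distributed material". Under Cognitive Aspects, "Information is given about the disease so the patients can get to know it better". That section adds an audiovisual presentation, a written dossier, and answers to the patient's doubts at follow-up. Under Follow up, the control group's visits are described as measurement and data recording only.

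Under Statistical Analysis, the primary outcome is to be compared by a chi-square test, with relative and absolute risk reduction, NNT and a logistic regression on adherence (yes/no). That section does not say which of the three measures these refer to.

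**The concern.** A measure of adherence should change only if the taking of doses changes. As described, the Batalla result contains no dose information: it turns on correct answers about the illness. The intervention supplies information on that subject to one arm. A taught patient could therefore move from non-adherent to good adherent on this measure while using the inhaler exactly as before.

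Randomisation does not remove such an effect, because the teaching comes after allocation and differs by arm. A larger sample would only make the difference easier to detect. Any distortion would run towards the intervention.

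At stake is how a split result would be reported. If Batalla improved and the dose/pill count did not, the plan as written would allow the Batalla result to be presented as a gain on the primary outcome, with a risk reduction and an NNT attached.

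**Working it through.** **1. The texts side by side.**

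| Link | Where it stands | Stated or inferred |
|---|---|---|
| Batalla measures knowledge of the illness | Primary outcome | stated |
| All three answers right = good adherent | Primary outcome | stated |
| It is one of three primary measures, each taken separately | Primary outcome | stated |
| The intervention arm is taught about disease and treatment | Group session; Cognitive Aspects | stated |
| Controls get no equivalent teaching | Follow up, Control Group | inferred: none is described |
| The teaching covers what the three questions ask | none | inferred: the questions are not shown |
| Chi-square, RRR, ARR, NNT and logistic model use the dose/pill count only | Statistical Analysis | not stated |

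**2. The plan's own figure.** The Sample size section gives 140 patients for a 25% difference (read as percentage points), 80% power, 95% confidence and 15% losses. It gives no control rate. I take 50%, the average adherence to long-term therapy cited in Background, and a two-sided 0.05 test, since sidedness is not stated.

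n per arm = [1.96·√(2·p̄·(1−p̄)) + 0.8416·√(p₁(1−p₁) + p₂(1−p₂))]² / (p₂−p₁)²

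With p₁ = 0.50, p₂ = 0.75 and p̄ = 0.625: [1.96 × 0.6847 + 0.8416 × 0.6614]² / 0.0625 = 57.7, so 58 per arm and 116 in total. 116 / 0.85 = 136.5, so 137. That is within 3% of 140. Other control rates do as well (25% also gives 137; 30% and 45% give 144), so the figure does not identify the control rate. It serves only to confirm the formula and the number evaluable: 140 × 0.85 / 2 = 59.5 per arm.

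**3. What teaching alone could do to the Batalla comparison.** Suppose intake is the same in both arms, and teaching turns a share t of those who would have failed the test into passers. With control pass rate p₁, the taught arm passes at p₂ = p₁ + (1 − p₁)·t. The chance of a significant difference is

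Φ{ [ (p₂−p₁)·√n − 1.96·√(2·p̄·(1−p̄)) ] / √(p₁(1−p₁) + p₂(1−p₂)) }, with n = 59.5.

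For p₁ = 0.50 and t = 0.2, p₂ = 0.60: (0.10 × 7.714 − 1.96 × 0.7036) / 0.7 = −0.87, and Φ = 0.19. For t = 0.5, p₂ = 0.75: (0.25 × 7.714 − 1.96 × 0.6847) / 0.6614 = 0.89, and Φ = 0.81.

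| Control pass rate (assumed) | t = 0.2 | t = 0.3 | t = 0.4 | t = 0.5 |
|---|---|---|---|---|
| 20% | 0.49 | 0.81 | 0.96 | 1.00 (0.997) |
| 30% | 0.35 | 0.65 | 0.88 | 0.98 |
| 40% | 0.26 | 0.50 | 0.75 | 0.92 |
| 50% | 0.19 | 0.38 | 0.61 | 0.81 |
| 60% | 0.15 | 0.28 | 0.46 | 0.67 |

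With no teaching effect (t = 0) the chance would be the nominal 0.05. The protocol gives no Batalla pass rate and no expected gain in knowledge, so every row is an illustration. The cell for 50% and t = 0.5 is the planned 25-point difference itself. Its 0.81 is therefore the design power restated, and is no evidence that teaching has so large an effect.

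**The case against.** The strongest reply is that the protocol already has a safeguard. It names the dose/pill count as the reference, says it trusts that method most, and keeps the three measures apart. A Batalla gain cannot leak into the dose-count result, and a gain on Batalla alone would be visible to a reader. The article also says openly what the test measures and why it is kept: ease of use in practice, and acceptable validity in the team's earlier work. All of this stands, and it limits the harm. It does not remove it, because Batalla remains a primary adherence measure in its own right and the analyses are not tied to the count.

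The validity argument carries less weight. Background reports that Batalla and Morisky-Green were most reliable when used together; here each is used alone. The Primary outcome section itself limits the validity to certain circumstances.

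Three stronger readings are tempting, and the documents do not support them.

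- A reader might infer that a Batalla difference would show nothing but remembered teaching, so that bias is certain. The protocol's premise is that cognitive aspects influence adherence, so better knowledge could accompany a real change in intake. The questions are also not shown.
- A reader might infer that the earlier validation cannot apply to the taught arm. That is plausible, since teaching a correlate of behaviour can break the correlation, but the article does not say what the earlier cohorts were told.
- A reader might infer that controls receive no information at all. The article describes none for them, but does not say what usual primary care provides.

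A parallel worry about Morisky-Green, that it records attitude by self-report while the motivational component works on attitudes, is weaker. The point does not depend on it.

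**Conclusion.** The concern holds as a possibility that the plan leaves open, not as a demonstrated bias. A knowledge test stands as a separate primary measure of adherence, in a trial whose intervention gives information on the same subject. A difference on it may partly or wholly reflect learning, in favour of the intervention.

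The size cannot be determined from the documents. At an assumed 50% control pass rate and no change in intake, the chance of a significant Batalla difference runs from about 0.19 to 0.81 as teaching converts 20% to 50% of would-be failures; lower control pass rates raise it and a 60% rate lowers it. These figures rest on 59.5 evaluable patients per arm, a two-sided 0.05 test without continuity correction, and overlap between the questions and the teaching.

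The dose/pill count is not affected by this mechanism. The change is worth making because it follows the protocol's own ranking of the three measures and costs little.

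**What to change.** State the dose/pill count (80% to 110% of prescribed doses, as already defined) as the sole primary outcome. Name it in Statistical Analysis as the basis for the chi-square test, RRR, ARR, NNT and logistic model. Report the Batalla test as a knowledge (process) measure, and the Morisky-Green test as a secondary self-report measure of adherence.

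The cost is an amendment to the primary outcome wording of an ethics-approved, registered trial, and the loss of primary status for the two self-report tests. Both questionnaires stay in use, and no new data are needed.
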